### START mHealth application

Those randomized to receive the app have an account created by the START staff member, are asked to download the app, and are given a START app tutorial during their onboarding visit. Participants are instructed to log into the app and are guided through the Check-Ins, Welcome Videos, My Settings page, Crisis Resources, Skills, Self-Care Check List and other key components (Table 1). Participants are asked to begin the first lesson, Positive Events and Gratitude, and make their way through each lesson on the app as it unlocks. If they have any questions, they are encouraged to reach out to START staff via text or email. Additionally, they are asked to engage with the app several times per week for six months.

**Table 1 Tab1:** START intervention app components and features

Features	Description	Format	Activities
Check-In	Check in on mood, adherence, using drugs/alcohol	Text, graphics	Prompts participant to choose current mood, report if they took their HIV medications yet, and report if they are currently using drugs/alcohol.
Welcome	Introduction to the START app and investigators, self-care, and information about stimulant use and HIV	Text, graphics, video	Choose self-care strategies to implement when stressed
Positive Events and Gratitude	Noticing positive events, developing gratitude	Text, graphics, video	● Write down 3 good things that happened today ● Write down 1 + thing that the participant is grateful for ● Meditation – Breath retraining
Mindfulness and Self-Compassion	Informal mindfulness, self-compassion	Text, graphics, video	● Write down 1 + things that participant wants to be mindful of ● Choose the self-compassionate statement in 4 multiple choice scenarios; practice using self-compassion skills on personal situations ● Meditation – Mindful breathing
Reappraisal and Coping	Learning positive reappraisal and coping skills	Text, graphics, video	● Choose the positive reappraisal statement in 3 multiple choice scenarios; practice using positive reappraisals on personal situations Meditation – Mountain meditation
Values, Strengths, and Goals	Taking inventory of values and strengths; applying values and strengths to setting goals	Text, graphics, video	● Practice on 2 scenarios to set an attainable goal, ordering steps to achieve goal, and attaching values and strengths ● Set own attainable goal, setting steps, and attaching values and strengths, track during check in. ● Meditation- Mindful meditation

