### Informational control website

START participants randomized into the control arm of the study will have access to the START Study website. The goal of the website is to provide participants with resources in four distinct categories: crisis resources, LGBTQ resources, mental health and substance use resources, and HIV and health resources. Resources include website access, phone numbers to call, and lines to text depending on contact preference.

Crisis Resources include 988 Suicide and Crisis Lifeline, Crisis Text Line, THRIVE Lifeline, and The Trevor Project Lifeline. These crisis resources offer access to local crisis centers that provide free and confidential emotional support to people in suicidal crisis or emotional distress 24 h a day, 7 days a week.

LGBTQ Resources include LGBT National Help Center, LGBT Near Me, CenterLink, Centers for Disease Control and Prevention, and TrevorSpace. These resources provide free and confidential peer support, information, and referrals to local resources.

Mental Health and Substance Use Resources include National Institute of Mental Health, The National Alliance on Mental Illness, Mental Health America, Substance Abuse and Mental Health Services Administration, and North American Syringe Exchange Network. These resources provide information about mental health for LGBTQ people, important risk factors, and finding help for mental health and substance use.

HIV and Health Resources include Health Resources and Services Administration, The Body, Greater than AIDS, Be in the KNOW, and POZ. These resources provide information about locating local HIV providers, HIV/AIDS related information and support, and access to the latest information, news, and community forums regarding the needs of people living with and affected by HIV/AIDS. Participants are encouraged to visit the control website as often or as little as they would like and to reach out to any of the resources when needed.

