2.1.Weekly analysis and reporting on Treatment Group activity: Study staff assigned to engagement reporting reviews daily email from intervention app developer, Radiant, listing study participants assigned to the treatment group who have not opened the intervention (app) for 15 days or more. Using a coordinator account, staff then accesses backend user reports on the app developer’s website to review inactive participants’ check-in data against the dates they opened the app to ensure accuracy. If a discrepancy is noted in these reports, staff reaches out to the app developer to investigate potential tech issues.2.2.Weekly Coordinator Reports and participant outreach: Study staff assigned to engagement reporting reviews all backend user reports on the app developer’s website to track activity of each participant assigned to the Treatment Group in each activity and each module, number of reminders set, and number of videos watched. Each study coordinator receives a full weekly report on all activities of those who have been inactive 15 days or more, with recommendations for outreach suggesting activities the participant has not yet tried or any emerging or recurring patterns that may be useful to the coordinator. Coordinators reach out to participants on this weekly report by text or email to ask if the participant is having any trouble with the app and to suggest news ways to engage. When participants reply with tech issues, such as a forgotten PIN number or new phone, study coordinators help the user resolve the issue and re-engage with the study intervention.2.3.Monthly Engagement Report: The same procedures that are done weekly for Inactive Users are applied to all participants assigned to the Treatment Group once a month, including both active and inactive. Discrepancies are reported to the app developer to identify potential reporting errors or tech issues, and the project coordinator and engagement staff meet with the developer on a regular half-hour weekly video conference call to investigate and address these issues. Coordinators are notified of any issues involving their participants that have been brought to the app developer. Each month, study coordinators are sent a full report on the check-in activity and time in app (times opened) for all their participants, with more detailed notes on individual engagement to personalize their interactions with participants.2.4.Month-to-month comparison for optimization: The activities of all participants in the treatment group during the current month is compared to their cumulative activity reported the previous month, noting any significant changes in engagement for each participant. Coordinators receive specific recommendations for outreach to their study participants in order to optimize engagement, highlighting those whose engagement has notably decreased in the past month.2.5.The project coordinator is notified by direct message with an executive summary of any noteworthy overall trends or discrepancies. The executive summary and any action items are also shared at the next weekly START Team meeting.2.6.Documentation of Engagement: Past engagement reports are stored in study staff shared drive. In addition to being communicated directly, study staff have access to these shared weekly and monthly engagement reports.

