We plan to test these longitudinal hypotheses and will model outcomes using multilevel random coefficient models (i.e., hierarchical linear modeling; HLM). These models incorporate random intercepts and slopes for each participant based on the participant’s multiple measurements over time [93]. Initial models will follow an intent-to-treat (ITT) approach and compare outcome trajectories for participants in START intervention and informational control condition across time via the group-by-time interaction effect. A priori planned comparisons to address Hypotheses 1a–1b (d) will be performed to test group differences at 6 and 12 months. These planned comparisons will be evaluated at α = 0.05; any subsequent post-hoc comparisons will be adjusted via simulation-based stepdown methods to maintain a nominal Type 1 error rate of 0.05. Multilevel models for continuous outcomes (e.g., positive affect) will be fitted to the data using SAS PROC MIXED [94]. Multilevel models for ordered categorical or binary outcomes (e.g., probability of urine reactive urine toxicology for stimulants and sex risk) will be fitted using SAS PROC GLIMMIX with maximum likelihood estimation via adaptive quadrature with a minimum of 15 integration points [95]. Additional exploratory analyses will investigate moderators of the direct effects of the intervention on ART adherence and viral suppression. Random coefficient models to address hypotheses 1a-1b (d) will be extended to explore moderation by including moderator-by-intervention group and moderator-by-moderator product terms. Secondary analyses will also explore whether the potential mechanisms of change (e.g., reduced stimulant use) mediate the effects of START on ART adherence and viral suppression using the contrast weight-based approach of Kenny for assessing mediation in multilevel models [96]. Multilevel model assumptions (e.g., normal, homoscedastic variances) will be checked; data that do not conform to heteroskedastic-consistent estimators will be substituted for model-based estimators [97].

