Secondary analyses will estimate the association between individual features of the START intervention (e.g., number of logins, days self-reported ART, number of modules completed) with ART adherence and VL suppression. These components of the intervention will be treated as predictor variables in regression models with the previously described ART adherence and VL suppression measures the dependent variables. The analytic approach for these secondary analyses will follow those for the primary aims, with regression models (linear or logistic) containing intervention arm as the primary independent variable and adjust for any necessary demographic factors.

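### The app-feature regressions keep trial arm as lead predictor although controls have no app, so the arm coefficient is not the intervention effect, and the feature slopes are adjusted for demographics alone

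*Protocol article*

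**What the plan says.** The last paragraph of Statistical analyses (under Aim 1b) sets out secondary analyses of "individual features of the START intervention (e.g., number of logins, days self-reported ART, number of modules completed", with ART adherence and viral suppression as outcomes. It says that "These components of the intervention will be treated as predictor variables in regression models". It continues: "The analytic approach for these secondary analyses will follow those for the primary aims". On the form of these models, the same sentence gives arm the leading place: "regression models (linear or logistic) containing intervention arm as the primary independent variable and adjust for any necessary demographic factors". The second statement refers back to the feature analyses just described, so its natural reading puts the features and arm in one model. The paragraph neither limits the fit to START participants nor says what value controls take on the features.

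Other sections show who can have app use. Under START mHealth application: "Those randomized to receive the app have an account created by the START staff member". Under Informational control website: "START participants randomized into the control arm of the study will have access to the START Study website". Under Study Retention, staff use back-end reports to "track activity of each participant assigned to the Treatment Group in each activity and each module". No app use is recorded for controls, because they have no app.

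The effect of START itself is tested elsewhere in the same section: "Initial models will follow an intent-to-treat (ITT) approach", with planned comparisons at 6 and 12 months.

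**The concern.** A coefficient described as the main one in a model will be read as the effect of the intervention. Here it cannot be that, because the other predictors exist in one arm only and are measured after randomisation. An effective app could show a null arm term, and an app with no effect could show a harmful one.

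The feature slopes will be read as evidence about which parts of the app work. Use of an app is self-selected, and the plan names only demographic factors for adjustment. The Background reports that stimulant use goes with lower adherence and unsuppressed viral load, so prognosis at entry matters for these outcomes. If it also governs how much a man uses the app, the slope carries that link.

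One example feature also overlaps with an outcome. Table 1 describes a check-in where the user reports whether he has taken his HIV medication. Counting such days and using them to predict the self-reported adherence scales partly regresses a construct on itself.

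**Working it through.** The article states no figure for this analysis, so there is none to reproduce. The check is of model structure, followed by an illustration.

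**1. Controls coded 0.** Let x be a feature, with x = 0 for every control, and fit y on arm and x by least squares without covariates. Controls fix only the intercept, and START participants fix their own line. So:

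- feature slope b = slope of y on x within START;
- arm coefficient = (mean y in START - b × mean x in START) - mean y in controls = total arm effect - b × mean x in START.

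The arm coefficient is therefore the fitted START outcome at zero use minus the control mean. The logistic model without covariates splits in the same way, on the log-odds scale.

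**2. Controls left missing.** Complete-case fitting drops every control. Arm is then constant, and the design matrix (intercept, arm, feature) has rank 2 of 3, so arm is not estimable. Imputation does not help, because app use by men without an account is undefined rather than unobserved.

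**3. Illustration with zero coding.** From Power and sample size: 72% suppression in controls and 89% in START, a 17-point difference. Assumed, and not in the article: 0 to 5 modules completed (Table 1 lists five skills lessons), mean about 3, and the links between prognosis and use given below. Large-sample simulation, N = 400,000:

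| Assumed truth | Arm alone: risk difference (OR) | Slope per module | Mean modules | Arm with modules: risk difference (OR) |
|---|---|---|---|---|
| 17-point effect wholly through modules | 0.170 (3.14) | 0.057 | 3.00 | 0.00 (0.64) |
| No effect; use is prognostic | -0.001 (1.00) | 0.048 | 2.91 | -0.141 (0.51) |
| Uniform 17-point effect; use is prognostic | 0.168 (3.09) | 0.025 | 2.91 | 0.095 (1.57) |

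In rows 2 and 3 the log-odds of completing a module is 0.4 plus a standard normal prognosis score. Suppression probability rises by 0.10 (row 2) or 0.05 (row 3) per SD of that score.

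The formula in step 1 reproduces the last column: 0.170 - 0.057 × 3.00 = -0.001; -0.001 - 0.048 × 2.91 = -0.141; 0.168 - 0.025 × 2.91 = 0.095.

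**4. Range.** With no true effect and a mean of 2.91 modules, the arm coefficient is -b × 2.91: 0 for b = 0, -0.03 for b = 0.01, -0.07 for b = 0.025 and -0.14 for b = 0.048. The size depends entirely on b and mean use, which the article does not give.

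**5. Precision.** Take a continuous outcome with SD 1, 140 per arm (the article's effective number) and modules with mean 3 and variance 5 × 0.6 × 0.4 = 1.2 in START. The arm SE is √(2/140) = 0.12 without modules. With modules it is √[(2 + 3²/1.2)/140] = √(9.5/140) = 0.26. Simulation gave 0.119 and 0.262, a ratio of about 2.2. The ratio does not depend on the number per arm.

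**6. Adjustment variables available.** Table 2 schedules viral load, both adherence measures and stimulant use at the first baseline assessment. Treatment seeking is the stratification factor under Randomization and onboarding. Nothing new has to be collected.

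**The case against.** The stated aim of the paragraph is an association between features and outcomes. The intervention effect comes from the intent-to-treat models. A reader might infer that the tests of Hypotheses 1a and 1b are compromised; they are not, because those models contain no engagement term. This objection stands in full.

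A reader might also infer that the arm term spoils the feature slope. Step 1 shows otherwise: without covariates the slope is the within-START slope with or without arm. The confounding would equally affect a START-only fit adjusted for demographics alone. This stands too, so the confounding is a separate weakness from the arm term.

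Zero coding is not stated, and the closing sentence may be carried over from the primary-aim text with separate fits intended. That is possible, but the article does not say so, and under missing coding the arm term it calls for disappears. Exact covariates are often left to the analysis plan; here, however, the article names the kind of adjustment and confines it to demographics.

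The circularity is narrow. It concerns one example feature against self-reported adherence only. The Wilson and VAS scales are separate survey measures, so the overlap is partial, and viral suppression from dried blood spots is not affected.

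**Conclusion.** The concern holds for a secondary, associational analysis. As worded, the arm coefficient in the feature models is either START at zero use versus control or not estimable, and in neither case the intervention effect. This follows from the article's own account of who has the app and needs no assumption about engagement.

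The feature slopes are open to confounding by baseline prognosis, because only demographic factors are named. How strong that is depends on how far prognosis drives app use, which the article does not report.

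A reader might want a single figure for the distortion. The documents do not support one: the values in the table rest on an assumed engagement distribution and assumed links to outcome, and the range includes zero. A reader might also think that randomisation could serve as an instrument for the features. One binary instrument cannot identify the effects of several features.

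The point deserves correction because these results would be used to judge app components. No confirmatory result changes.

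**What to change.** Reword the last paragraph of Statistical analyses:

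- Fit the feature analyses in START participants only, with no arm term.
- Adjust for baseline viral load, baseline adherence, baseline stimulant severity and the treatment-seeking stratum, besides any demographic factors.
- Do not use in-app ART days to predict self-reported adherence. They may stay as a predictor of viral suppression.
- State that arm effects are taken only from the intent-to-treat models. Keep the existing description of the feature results as associations.

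The cost is a change of wording; no new data are needed. The START-only sample is smaller, but controls carry no information on the slope of a feature they cannot have. With covariates in the model, they would help only to estimate the covariate coefficients.

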### Power and sample size

Power analyses, using PROC POWER in SAS 9.4, were conducted to support Aim 1a Hypothesis 1 (i.e., men who are in the active START group will have greater VL suppression at 6 months compared to the control group). Treatment effects for the intervention and control groups were estimated using the observed six-month viral suppression success rates from the RCT of ARTEMIS. That is, the virus suppression rate will approximate 29/45 = 64% (80% CL: 55–73) for untreated men and 40/42 = 95% (80% CL: 89–98) for treated. To account for the uncertainty in those estimates, the pessimistic (most similar) percentage estimates from 80% Agresti-Coull confidence limits (72 vs. 89%) were used to estimate the effect for the untreated and treated groups. Beginning with 175 men per group and assuming an attrition rate of no more than 20% (effective N at six months of 140), we have approximately 90% power to detect a statistically significant difference with an alpha error rate of 5% using a two-sided Fisher’s Exact test for the two proportions at six months. This is sufficient statistical power to detect a difference in VL suppression as low as 16% between the START intervention and informational control conditions at 6 months. Even with 70% retention, power remains above 85% for detecting an effect of START on VL suppression.

### Economic evaluation

Accurate economic data is necessary for making informed decisions about implementing protocols, assessing budget impact, identifying financial or resource barriers to implementation, and ensuring fiscal sustainability over time. Our team will gather comprehensive information on the resources used and the associated costs of providing the intervention during the RCT of START. This is crucial for ensuring the success of our project and achieving our desired outcomes. Gathering economic data beforehand enables a more accurate micro-costing analysis of intervention costs and comparison with the control condition. This helps to identify any financial or resource barriers to implementation. The unique aspect of mHealth interventions is that they require a significant upfront investment to develop and launch the platform, but once established, the ongoing costs per participant are relatively low.

We will be comparing the cost of implementing START to the control conditions from the provider perspective. This analytic perspective will determine the resources that are relevant for the cost analysis, such as direct costs of service delivery for providers and reimbursement rates for payers. We will be obtaining cost information from annual budgets and financial reports, excluding any costs that are specific to research rather than clinical/monitoring activities. The goal is to accurately calculate the expenses of providing START. This will help stakeholders decide if it is possible to expand its implementation with the current resources and reimbursement methods.

To implement START, there are several expenses to consider. These include start-up/training costs, personnel expenses (including fringe benefits), contracted services, consulting services, supplies and equipment, and administrative costs. Consulting services may not apply in all situations. In our analysis, we will include the cost of sending and processing DBS samples. As part of a sensitivity analysis, we will examine how total implementation costs change if such expenditures are not factored in. The key economic data for both scenarios will include the *total yearly expenses*, the *differential costs between START and the control group*, and the *average yearly expense per participant*.

The cost data will be used to conduct a cost-effectiveness analysis (CEA) of START. This analysis will determine the additional cost required to achieve viral suppression at six and twelve months in START compared to the control group. The economic analysis will also evaluate the broader impact on the health sector by examining changes in non-study medical services utilization and costs for general medical care, HIV care, and behavioral health care. As part of the main trial outcome assessments, male participants will report their healthcare utilization services in the past six months, which will include emergency department visits, urgent care visits, inpatient hospital nights, HIV primary care appointments, and number of blood draws for HIV disease markers (CD4 + count and viral load). As part of the evaluation of START, we will systematically assess utilization of mental health and substance use disorder treatment services, such as individual and group counseling sessions, inpatient treatment nights, outpatient treatment days, and 12-step meeting attendance. We can convert counts of different types of physical and behavioral health services into dollars using monetary conversion factors. It is important to note that a visit to the emergency department can cost $2,996 on average. In contrast, a night spent in residential substance use treatment costs $177 on average. By reducing the use of healthcare services that are unnecessary, this will generate a significant reduction in costs to the health sector, which will be captured as part of the economic evaluation of START.

Finding the most cost-effective interventions can be challenging, but a CEA can be used to calculate the incremental difference in costs and outcomes between two or more alternative interventions. For instance, one can compare the cost of a new intervention to the cost of usual care and assess differences in core clinical measures such as medication adherence or retention in care. The resulting information can be used to identify the more cost-effective intervention, with a lower cost-effectiveness ratio. The analysis calculates the incremental cost-effectiveness ration to assess the additional cost per unit of desired outcome in an experimental condition relative to a control condition. We will perform sensitivity analyses to determine the impact of different cost estimates (for example, assuming that costs will decrease over time as a result of economies of scale) and outcome parameters (such as changes in the rates of viral suppression or the ability to maintain viral suppression during follow-up) on the cost-effectiveness results.

